**Fig. 2 Fig2:**
[figure not shown]
Daily adjustment of PN rate in intervention arm. ECMO: extracorporeal membrane oxygenation; EN: enteral nutrition; PN: parenteral nutrition; RRT: renal replacement therapy

Management of interruptions to EN in the intervention arm:In the event of an anticipated or actual interruption to EN for a period of 2 hours or more in the intervention arm, the interventional strategy will be adjusted to minimise energy deficit for the period of the interruption. During the interruption period, the intervention will be run at the hourly rate corresponding to 20 kcal/kg or 24 kcal/kg for those on RRT and/or ECMO. If the patient is already receiving the highest rate of the intervention, there will be no change to the rate during the interruption period. As soon as is practical, EN should be recommenced as per local protocol and the intervention returned to the rate determined as per the midday assessment.

Cessation of study intervention prior to the end of the study period:The intervention will cease either prior to ICU discharge or 7 days following enrolment if energy from EN and non-nutritional sources provides more than 80 % of estimated energy requirements on any day. Cessation on any one day will not preclude recommencement in the following 24 hours should the strategy be indicated based on the procedures previously outlined, until study day 7.Should a patient commence oral intake during the 7-day study period, the intervention will cease when it is deemed that the patient will resume oral intake with the intent to provide nutrition, that is, not only to provide water or fluid intake.

### Usual care arm

After enrolment, patients allocated to the usual care arm will commence or continue EN via an enteral tube to a target rate aimed to provide 100 % of daily energy requirements. All other aspects of nutrition therapy will be managed according to local unit protocol and, if required, include the use of promotility agents and the placement of nasojejunal feeding tubes prior to commencement of PN. PN will only be used in the usual care arm if the above methods have been attempted, or if an absolute contraindication to EN develops. The interventional product will be used in the usual care arm should PN be required within 7 days of randomisation. If PN is required after study day 7, it will be the usual hospital PN formula, managed by the treating clinicians as clinically appropriate.

### Outcome measures

The primary outcome of this trial is the mean energy amount in calories delivered from nutrition therapy over the first 7 days of the study period.

Secondary outcomes include:Total protein amount delivered in the first 7 days of the study periodTotal energy amount delivered in the ICU stay (up to 28 days)Total protein amount delivered in the ICU stay (up to 28 days)Total antibiotic usageSequential Organ Failure Assessment scoresDuration of mechanical ventilationDuration of ICU and hospital stayMortality to 180 days post randomisationFunctional and quality of life to 180 days post randomisation

### Study management and data collection

This trial will be coordinated by the Australian and New Zealand Intensive Care Research Centre (ANZIC-RC), Monash University, Melbourne, Australia. Dedicated study tools will be provided to participating sites to standardise all study procedures. Data will be collected at each site by dedicated and trained research staff using a paper case report form. Study variables collected will include baseline demographics such as anthropometric measurements, admission diagnoses, physiological parameters, Acute Physiology and Chromic Health Evaluation II, daily information including nutrition therapy, antibiotic use, blood tests and outcome data such as mortality, protocol deviations and serious adverse events (SAEs). At ICU and hospital discharge, functional, strength and health-related quality of life (HRQOL) assessments will be undertaken using the 6-minute walk test if possible and/or the highest level of function scale [19], hand grip strength and the EuroQol 5 dimension 5 level (EQ-5D-5 L) tools, respectively. Study participants will be contacted at 90 and 180 days post randomisation (unless previously deceased) to assess HRQOL, resource utilisation and survival. Follow-up assessments will be conducted via telephone by the research staff at the randomising site using a pre-prepared script to obtain the assessment using the EQ-5D-5 L. In the event that the patient is unable to complete the assessment at any time point, a relative or friend for the patient will be used as per the instructions for the EQ-5D-5 L. Data will be entered by the research staff at each participating site into a web-based database developed by Spiral Web Solutions, Wellington, New Zealand. Table 1 details the full table of events from baseline to outcome assessment.

**Table 1 Tab1:** Table of events: usual care and intervention arms

Study day	Baseline	1	2	3	4	5	6	7	8	9	10	11	12	13	14	21	28	ICU D/C	Ward	Hospital D/C	90 days post D/C	180 days post D/C
Incl. and excl. criteria	X																					
Consent	X																					
Randomisation	X																					
Demographics	X																					
Apache II score	X																					
Apache III diagnosis	X																					
Daily data^a^ (ICU)	X	X	X	X	X	X	X	X	X	X	X	X	X	X	X	X	X					
LFTs, WBC	X	x	x	x	x	x	x	X	x	x	x	x	x	x	X	X	X					
Use of new antibiotics	X	X	X	X	X	X	X	X	X	X	X	X	X	X	X	X	X					
SOFA score	X	X	X	X				X							X	X	X					
TG	X			X				X							X							
CRP	X							X							X		X					
Dur MV																		X				
LOS ICU																		X				
LOS hospital																				X		
Survival status																		X		X	X	X
Mid-upper arm muscle circumference	X									Measured once patient is ready for ICU D/C										X		
Hand grip										Measured once patient is ready for ICU D/C										X		
6-minute walk test																				X		
QOL																				X	X	X

X denotes must be collected on specified day

x denotes collect only if measured, no need to specially collect

Abbreviations used in table: *CRP* C-reactive protein, *EN* enteral nutrition, *ICU* intensive care unit, *LOS* length of stay, *MV* mechanical ventilation, *PN* parenteral nutrition, *QOL* quality of life, *SOFA* Sequential Organ Failure Assessment, *TG* triglycerides

^a^Daily data: The following variables will be collected daily: target energy and protein requirements, received energy and protein amounts, received EN and PN volumes, AM BGL levels, units of insulin delivered, gastric residual volumes, documented episodes of vomiting, documented episode of abdominal distension, documented episode of witnessed aspiration

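### Table 1 counts the 90- and 180-day contacts from discharge, while the abstract, outcomes and text count them from randomisation; quality-of-life timing is what is exposed

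*Protocol article*

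**What the plan says.** Three places in the protocol article count late follow-up from randomisation.

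- Abstract, Methods/design: quality of life, resource use and survival are followed up at 90 and 180 days after randomisation.
- Outcome measures: mortality, and function with quality of life, are secondary outcomes that each run to day 180 after randomisation.
- Study management and data collection: "Study participants will be contacted at 90 and 180 days post randomisation (unless previously deceased"), with quality of life, resource use and survival assessed at each contact.

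Table 1, in that last section, heads its two final columns "90 days post D/C" and "180 days post D/C". The rows for "Survival status" and for QOL carry a capital X in both. The footnote defines the mark: "X denotes must be collected on specified day". The text introduces the table in these terms: "Table 1 details the full table of events from baseline to outcome assessment".

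On discharge assessments the text says: "At ICU and hospital discharge, functional, strength and health-related quality of life (HRQOL) assessments will be undertaken". The QOL row of Table 1 has marks at hospital discharge and in the two late columns, and none at ICU discharge.

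**The concern.** One pair of contacts has two time origins, and both are current text. The difference matters because discharge happens after randomisation and the treatment may influence it; ICU and hospital stay are themselves secondary outcomes. On a discharge clock, a long-stay patient is assessed later after randomisation than a short-stay patient. If stay differed between arms, the time of assessment would differ between arms by the same amount. The outcome would then no longer be quality of life at 90 and 180 days after randomisation, as the outcome list defines it.

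A health-status questionnaire describes the day on which it is answered. An EQ-5D-5L taken on the wrong day cannot be moved back afterwards. The Sample size and power section also expects the secondary outcomes to inform later, larger trials, so their time point should be unambiguous.

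**Working it through.** This point has no stated figure to reproduce. The check is a comparison of time origins, followed by simple addition.

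**Step 1: set the statements side by side.**

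| Place | Item | Clock starts at |
|---|---|---|
| Abstract, Methods/design | quality of life, resource use, survival | randomisation |
| Outcome measures | mortality; function and quality of life | randomisation |
| Study management and data collection, text | quality of life, resource use, survival | randomisation |
| Table 1, last two columns | survival status, QOL | discharge |

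The abbreviation D/C also appears in the table's columns for ICU and for hospital discharge, so it means discharge. The two late columns do not say which discharge is meant.

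**Step 2: size of the shift.** Let L be the days from randomisation to discharge. Under the text the contacts fall at days 90 and 180 for everyone. Under Table 1 they fall at 90 + L and 180 + L. The article gives no value for L, so these are assumed values:

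| L (assumed) | 90 + L | 180 + L |
|---|---|---|
| 10 | 100 | 190 |
| 28 | 118 | 208 |
| 60 | 150 | 240 |

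The shift equals L, so a difference of d days in mean L between arms becomes a difference of d days in mean assessment time. The article gives no d, and none is assumed here.

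**Step 3: patients still in hospital.** Until discharge L is unknown, and the table gives no contact date. If L exceeds 90, the table's first contact (90 + L) falls after day 180, which is when the text wants the second.

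**Step 4: mortality.** Discharge cannot precede randomisation, so L ≥ 0 and 180 + L ≥ 180. A status check on the table's clock therefore covers day 180 after randomisation, provided the date of death is recorded. Table 1 also marks survival status at ICU and at hospital discharge, so deaths in hospital are captured.

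**Step 5: ICU discharge.** The text and the abstract both place quality of life at ICU discharge and at hospital discharge. The QOL row has no mark at ICU discharge. The table is described as the full schedule, so this is a second mismatch between the two.

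**The case against.** The strongest reply is that the headings are a labelling slip. Three statements, including the outcome definitions that govern the analysis, agree on randomisation, and only two column labels disagree. That is probably right about which side is in error. It does not remove the contradiction, because the table declares its marks mandatory on the day that the heading names.

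Several stronger readings are tempting, and the article does not support them:

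- *Sites will schedule calls from Table 1, so different sites will collect different data.* The article does not say that sites work from this table. It mentions dedicated study tools, a paper case report form and a prepared telephone script, none of which is shown. The timing problem is conditional on the table being followed.
- *Survival follow-up becomes conditional on leaving hospital alive.* Survival status is also marked at both discharges, and day-180 mortality can be recovered from dates of death.
- *The 6-minute walk test is wrongly missing at ICU discharge.* The text makes this test conditional on feasibility and offers a function scale beside it or in its place. Leaving a mandatory mark off a test of that kind is no clear contradiction.
- *No functional test is scheduled up to day 180.* The outcome joins function and quality of life in one item with an outer limit. Which component is read at which time is detail that an article may leave to the full protocol.

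It is also fair to say that the range for L is an assumption and that no arm difference in stay is documented.

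**Conclusion.** The contradiction stands. Table 1 counts the two late contacts from an unspecified discharge, and the abstract, outcomes and text count them from randomisation. If the table were followed, the EQ-5D-5L would be delayed by each patient's own L. Under the assumed 10 to 60 days this means days 100–150 instead of 90, and days 190–240 instead of 180, with no defined date for a patient still in hospital. The missing ICU-discharge mark for quality of life is a second, smaller conflict.

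Severity is moderate. The affected items are secondary outcomes of a 100-patient phase II trial. The primary outcome, energy delivered over the first 7 days, is unaffected, and mortality to day 180 is little affected as long as dates of death are recorded. The article does not show that any contact has been or will be mistimed; it shows that its schedule, as written, would mistime the quality-of-life contacts.

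**What to change.** 1. Relabel the last two columns of Table 1 as 90 days post randomisation and 180 days post randomisation.
2. Reconcile the ICU-discharge entry for quality of life with the text: either add the mark to the table or remove that time point from the text and abstract.
3. Confirm that the case report form, the telephone script and the database compute the contact dates from the date of randomisation, and that dates of death are recorded.

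The cost is a corrected table, a short note to the six sites and a check of existing tools. Relabelling adds no procedure. If contacts have already been made on the discharge clock, their actual dates should be kept so that the time since randomisation is known at analysis.

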### Ethical considerations

The study protocol has been approved by The Alfred Hospital Ethics Committee in Australia and the Multi-Region Ethics Committee in New Zealand.

Participants in this trial will be unable to provide informed consent for themselves to participate in the study at the time of enrolment. A delayed consent model has been approved by the responsible ethics committees, which means a patient’s legal surrogate, relative/friend or whanau member will be approached for consent to participate in the study. Following consent from a patient’s legal surrogate, relative/friend or whanau member, the patient will be approached to give consent to continue in the trial if they recover the ability to do so and the timing is appropriate.

### Sample size and power

Using two published RCTs on nutrition therapy in ANZ critically ill patients, we estimated that the usual care group would receive an average of 1,400 kcal/day. We aim to deliver an additional 420 kcal/day (using a standard deviation of 600 kcal/day) to the intervention group, which is a 30 % relative increase in energy delivery and requires a sample size of 100 patients (80 % power, significance 0.05).

This sample size will also provide baseline rates of other key secondary outcomes which could be used in the future to inform sample size estimations for larger RCTs assessing clinical outcomes.

### Statistical analysis plan

Statisticians at the Australian and New Zealand Intensive Care Research Centre (ANZIC-RC) will perform statistical analysis using the intention-to-treat principle. All data will initially be assessed for normality and will be log-transformed as appropriate. Baseline variables and single measure outcomes will be compared using chi-square tests for equal proportion (or Fisher’s exact tests if numbers are small), Student’s *t*-test for normally distributed outcomes and Wilcoxon rank-sum tests otherwise. Continuously normally distributed repeated measure outcomes will be compared between groups using longitudinal mixed modelling fitting main effects for treatment and time with an interaction between treatment and time to determine if groups behave differently over time. Sensitivity analysis accounting for site, known covariates and baseline imbalances will also be performed for all outcomes, using logistic regression for binomial outcomes and mixed linear or non-linear modelling for continuous outcomes. Analysis will be performed using SAS version 9.4 (SAS Institute Inc., Cary, NC, USA), and a two-sided *p*-value of 0.05 will be considered statistically significant.

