**Methods/design:**

This prospective, multi-centre, randomised, stratified, parallel-group, controlled, phase II trial aims to determine whether a supplemental parenteral nutrition strategy will reliably and safely increase energy intake when compared to usual care. The study will be conducted for 100 critically ill adults with at least one organ system failure and evidence of insufficient enteral intake from six intensive care units in Australia and New Zealand. Enrolled patients will be allocated to either a supplemental parenteral nutrition strategy for 7 days post randomisation or to usual care with enteral nutrition. The primary outcome will be the average energy amount delivered from nutrition therapy over the first 7 days of the study period. Secondary outcomes include protein delivery for 7 days post randomisation; total energy and protein delivery, antibiotic use and organ failure rates (up to 28 days); duration of ventilation, length of intensive care unit and hospital stay. At both intensive care unit and hospital discharge strength and health-related quality of life assessments will be undertaken. Study participants will be followed up for health-related quality of life, resource utilisation and survival at 90 and 180 days post randomisation (unless death occurs first).

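### Ventilation time and length of stay are compared by t or rank test with no provision for death, so an arm with more deaths can appear to have shorter stays

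*Protocol article*

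**What the plan says.** The Outcome measures section lists duration of mechanical ventilation, duration of ICU and hospital stay, and mortality to 180 days as separate secondary outcomes. Table 1 records each duration once, at ICU or hospital discharge, so they are single-measure outcomes. Survival status is recorded at the same two points and again at 90 and 180 days.

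The Statistical analysis plan section has one general rule for all single-measure outcomes. Categorical ones get chi-square or Fisher's exact tests. Continuous ones get a t-test (after log transformation where appropriate) for "normally distributed outcomes and Wilcoxon rank-sum tests otherwise". The trial statisticians "will perform statistical analysis using the intention-to-treat principle", so patients who die stay in the comparison. The adjusted sensitivity analyses use "mixed linear or non-linear modelling for continuous outcomes". The section does not mention death in connection with any duration.

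**The concern.** The abstract describes the population as "critically ill adults with at least one organ system failure", and the inclusion criteria require mechanical ventilation at enrolment. Deaths during the ICU stay are to be expected. Death ends ventilation and stay just as recovery does, but it is the opposite outcome. A t or rank test on raw duration cannot tell the two apart: a patient who dies on day 3 supplies a value of 3 days, which ranks as better than a survivor discharged on day 10. Log transformation and the choice between t and Wilcoxon do not help, because the difficulty lies in what is measured and not in its distribution. Covariate adjustment does not help either.

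Two things are at stake. First, a between-arm difference in duration could be read as faster recovery when it reflects more or earlier deaths. Second, the Sample size and power section intends the trial to supply baseline rates of key secondary outcomes for planning larger trials, and a duration that pools survivors and non-survivors is a poor planning value.

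**Working it through.** **Inputs from the article.** Total sample 100, taken here as 50 per arm (equal allocation is assumed). Tests: t or Wilcoxon, two-sided 0.05, intention to treat. The article gives no mortality, stay or time-to-death figure, so there is no stated figure to reproduce and everything below is an assumed illustration.

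**Model A.** Stays are log-normal with log-SD 0.6, median 12 days in survivors and 6 days in those who die, the same in both arms. Only the mortality proportion m differs. The pooled median x solves

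m·Φ(ln(x/6)/0.6) + (1−m)·Φ(ln(x/12)/0.6) = 0.5

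- m = 0.2: x = 10.60, since 0.2 × 0.828 + 0.8 × 0.418 = 0.50
- m = 0.3: x = 9.88, since 0.3 × 0.797 + 0.7 × 0.373 = 0.50
- m = 0.4: x = 9.17, since 0.4 × 0.760 + 0.6 × 0.327 = 0.50

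The higher-mortality arm's median is therefore 10.60 − 9.88 = 0.7 days shorter at 20% v 30%, and 10.60 − 9.17 = 1.4 days shorter at 20% v 40%, although survivors' stay is identical.

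Simulating this model with 50 per arm gives the same shifts, against a between-trial SD of about 1.7 days for the difference in medians:

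| Mortality | Shift in median stay (days) | Wilcoxon significant in favour of the higher-mortality arm (nominal 2.5%) | Shift in median 28-day ICU-free days, death = 0 | Same arm favoured on ICU-free days |
|---|---|---|---|---|
| 20% v 30% | −0.7 | about 7% | −2.7 | 0.4% or less |
| 20% v 40% | −1.4 | about 17% | about −7 | 0.4% or less |

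**Model B, to test dependence on the assumptions.** Every patient has a stay drawn from one log-normal distribution (median 12 days, log-SD 0.7). Those who die have a log-normal time to death (median 5 days, log-SD 0.6), and the observed stay is the earlier of the two.

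- 20% v 30%: mean observed medians 10.0 v 9.0 days. The higher-mortality arm has the shorter median in 71% of trials and is declared significantly better by Wilcoxon in 8.6%.
- 20% v 40%: 10.0 v 8.0 days, 87% and 22.8%.
- The t-test on the log scale rejects at about the same rates (9.1% and 22.0%, both directions together).
- With deaths given the worst rank, the higher-mortality arm is declared better in 0.2% of trials or fewer.

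**Equal mortality.** With 20% in both arms and the same timing of deaths, Wilcoxon rejects in 4.3% of Model B trials, so its size is kept. The planning problem remains: in Model A the pooled median at 20% mortality is 10.6 days, against 12 in survivors. That is 1.4 days lower for a reason unrelated to recovery.

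**Chance imbalance.** At 20% mortality and 50 per arm, the standard error of the mortality difference is √(2 × 0.2 × 0.8 / 50) = 0.08. A 10-point gap can arise by chance. That does not inflate the error rate, but it can shape how this one trial's durations read.

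**The case against.** The strongest reply is that the article fixes less than the concern needs. Its test rule is generic, does not name ventilation or stay, and does not say how a patient who dies is coded. A condensed article may leave that to a fuller plan. One of the remedies, free days with death as 0, could even be analysed with the Wilcoxon test already listed. This stands in part. A reader might infer that the protocol lays down a rule under which death counts as a short stay. It does not: that step is inferred from raw durations, intention to treat and the named tests taken together. What remains is that the article names both the outcomes (raw durations) and the tests, and following them as written gives this result.

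The article also contains mitigation. Mortality is reported separately. Patients in whom death is imminent or highly likely within 96 hours, or who are unlikely to survive to 6 months, are excluded. This reduces early deaths without removing them, and a large mortality gap would be visible beside the durations.

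A reader might further infer that the direction of the stay comparison is likely to be wrong. The documents do not support that. It requires deaths to differ between arms in number or timing, and nothing in the article says that they will. Even a 10-point gap shifts the median by less than half of its between-trial SD (0.7 against 1.7 days). Nor does the article propose to carry a treatment difference in stay forward: it speaks of baseline rates that could be used for planning.

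Finally, free-day composites have the mirror-image weakness. In Model A survivors' stays are identical, yet ICU-free days differ by 2.7 or about 7, entirely because of mortality. That is correct and belongs with the fix.

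**Conclusion.** The point holds in a limited form. The stated tests, applied to raw durations of all randomised patients, make no provision for death and score early deaths as short stays. If deaths differ by arm, the comparison can favour the arm with more of them. Under Model A the median is about 0.7 to 1.4 days shorter, with a false significant advantage in about 7% to 17% of trials where 2.5% is nominal; Model B gives 1.0 to 2.0 days and 8.6% to 22.8%. All of these rest on assumed mortality and stay distributions and on the inference about how deaths enter. With equal mortality and timing the tests are valid, and only the usefulness of the raw durations for planning suffers.

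The primary outcome, energy delivered over 7 days, is not touched by this point, and no confirmatory claim rests on the durations. It is a worthwhile, inexpensive improvement to secondary outcomes of a 100-patient phase II trial.

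**What to change.** State in the analysis plan how death is handled in each duration outcome, by one of two routes:

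1. Compare time to live extubation, live ICU discharge and live hospital discharge, with death as a competing event (cumulative incidence by arm).
2. Compare days alive and free of ventilation, and of ICU, to day 28, with death scored 0, using the Wilcoxon test already planned.

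Under either route, tabulate raw durations separately for survivors and non-survivors as description without a test, and present them next to mortality.

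The cost is mainly wording. Table 1 already collects the durations, and survival status at ICU and hospital discharge. For route 2, the plan should also say how a death after discharge but before day 28 is identified, since Table 1 lists durations and status and not dates. The real drawback is interpretive: free-day composites are harder to read than days of stay and can be driven by mortality alone, so their components must be reported with them.

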### Randomisation, allocation concealment and blinding

Concealed randomisation will be performed via a web-based system which includes randomisation in blocks of 6 at each site. Treatment allocation will be stratified by site. The trial is unblinded.

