### Trial intervention and comparator

The intervention is the delivery of a supplemental PN strategy using Olimel N9-840E/Triomel 9, manufactured and supplied by Baxter Healthcare Corporation, Old Toongabbie NSW 2146, Australia. A multi-trace element solution (10 ml), multi-vitamin (Cernevit, Baxter Healthcare Corporation, 5 ml) and ascorbate (300 milligrams) for stability will be added to the intervention in a Baxter Healthcare Corporation compounding centre following good manufacturing practice.

Further details on the interventional product can be viewed at Additional file 1.

The comparator arm will be usual care, with provision and management of nutrition as per local practice at each participating site.

The intervention period is defined as 7 days from the day of randomisation.

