### Study procedures common to both arms

Patients will be screened for eligibility by research coordinators/medical staff at each site when they are between 48 and 72 hours of their first admission to the ICU. Those that are found to meet all the inclusion and none of the exclusion criteria will be randomised using a web-based randomisation system.

At randomisation, the body weight of study participants will be standardised using calculated body weight (CBW). To determine CBW, actual or estimated weight and height will be required to allow calculation of body mass index (BMI). The weight used to determine BMI will be defined according to the following hierarchy:Actual body weight if it has been recorded in the previous 6 weeksEstimated dry weight if actual weight is not known.

Height will be estimated using demi arm span [17].

CBW will be the patient’s actual weight if their BMI is deemed to be <25 kg/m^2^. If their BMI is ≥25 kg/m^2^, the CBW will be set to the patient’s ideal weight at a BMI of 23 kg/m^2^. Once the CBW has been determined, it will not be changed for the study duration.

Daily energy requirements will be estimated using CBW with a fixed prescription. The daily energy requirements will be set at 25 kcal/kg CBW unless the patient is receiving renal replacement therapy (RRT) and/or extracorporeal membrane therapy (ECMO), where 30 kcal/kg of CBW will be used. The daily energy requirement will only be changed during the study period if the patient commences or discontinues ECMO and/or RRT (with the two requirement options being 30 kcal/kg CBW or 25 kcal/kg CBW, respectively). A higher energy requirement has been chosen during RRT and/or ECMO due to the potential for increased metabolic stress and inflammation associated with the delivery of both therapies and the underlying disease processes that require these treatments [18]. Once randomised, the target rate for continuous EN delivery will be calculated by the treating clinical team to match the daily energy requirement, with the assumption that all patients should receive 100 % of their daily energy requirements from administration of EN and rounded up to the nearest 5 ml/hour. The choice of EN formula, protein requirement estimation and management of blood glucose levels will be according to local protocols.

Figure 1 demonstrates the study processes from screening to study completion.

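### Site, the stratification factor, is left out of the main comparison and a normality check can move the primary result off the kcal/day scale; the cost is modest, lost precision and an unfixed effect scale, and the repair is free

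*Protocol article*

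**What the plan says.** The section on randomisation in the Protocol article states "Treatment allocation will be stratified by site", with "randomisation in blocks of 6 at each site". Patients come "from six intensive care units in Australia and New Zealand". The comparator is "usual care, with provision and management of nutrition as per local practice at each participating site", so differences in feeding between sites are to be expected.

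The primary outcome, under Outcome measures, is "the mean energy amount in calories delivered from nutrition therapy over the first 7 days of the study period". That is one value per patient, in energy units. Sample size and power works on the same scale: usual care mean 1,400 kcal/day, difference 420, SD 600, 100 patients.

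The Statistical analysis plan section names no separate method for the primary outcome. Its general rule begins: "All data will initially be assessed for normality and will be log-transformed as appropriate". Single-measure outcomes then go to a t-test if normal and to a rank-sum test if not. Repeated measures get a mixed model containing treatment, time and their interaction. No main comparison contains site. It appears in one sentence: "Sensitivity analysis accounting for site, known covariates and baseline imbalances will also be performed for all outcomes".

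**The concern.** Two separate features of the main comparison do not fit the design.

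First, blocking within site balances the arms on site, so differences between sites largely cancel from the treatment contrast. An unadjusted test still counts that variation in its standard error. The interval is then wider than the design earns, and the p-value is too large on average.

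Second, the effect measure depends on how the data look. A t-test in kcal/day estimates a mean difference, a t-test on logs estimates a ratio of geometric means, and a rank-sum test concerns the probability that one patient receives more than another. The trial is meant to guide a larger one, and its planners will need the mean difference in kcal/day with a confidence interval. The text does not guarantee that this is the primary result.

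A baseline variable tied to the outcome by design is also absent from the main comparison: "Daily energy requirements will be estimated using CBW with a fixed prescription". The enteral target in both arms follows from that requirement, so it should explain some of the spread in absolute energy delivered.

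**Working it through.** **Inputs.** From Sample size and power: difference 420 kcal/day, SD 600, total 100, 80% power, alpha 0.05 (two-sided per the Statistical analysis plan section). From the randomisation section: blocks of 6 within site. Equal allocation, 50 per arm, is assumed because the ratio is not stated. The documents give no between-site variance, so the ICC (the share of the 600² variance lying between sites) is an assumption shown over a range.

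**The plan's own figure.** The stated inputs give 33 per arm, 66 in total, for 80% power, not 100. That mismatch is a separate matter. What counts here is that 50 per arm gives SE = 600 × √(2/50) = 120 kcal/day. Power for 420 is then Φ(420/120 − 1.96) = Φ(1.54) = 93.8% (exact t-test 93.4%).

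**Effect of leaving site out.** With site in the model, SE = 600 × √(1 − ICC) × √(2/50). The unadjusted test still uses about 120, so its true level is roughly 2 × [1 − Φ(1.96/√(1 − ICC))]. A simulation (six sites, blocks of 6, 102 patients, 4,000 runs per setting) checked both tests.

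| Assumed ICC | SE with site (kcal/day) | Unadjusted SE too large by | Level of unadjusted test, formula | Simulated level, unadjusted | Simulated level, with site | Power for 420, with site |
|---|---|---|---|---|---|---|
| 0 | 120.0 | 0% | 5.0% | 5.7% | 5.8% | 93.8% |
| 0.02 | 118.8 | 1% | 4.8% | 5.5% | 5.6% | 94.2% |
| 0.05 | 117.0 | 3% | 4.4% | 4.6% | 5.1% | 94.9% |
| 0.10 | 113.8 | 5% | 3.9% | 3.6% | 4.4% | 95.8% |
| 0.20 | 107.3 | 12% | 2.8% | 2.9% | 4.7% | 97.5% |

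The Monte Carlo error of a simulated 5% level is √(0.05 × 0.95/4,000) = 0.34 percentage points. The values above 5% in the first two rows are therefore within about two such errors of 5%, and the two tests agree there. From an ICC of 0.05 upward the unadjusted test falls below the adjusted one. Simulated unadjusted power for 420 kcal/day was 93.4% to 96.5% over these rows.

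**Effect of the normality check.** Take means of 1,400 and 1,820 with SD 600 in both arms.
- Raw scale: a difference of 420 kcal/day, an arithmetic ratio of 1820/1400 = 1.30.
- Log scale, if lognormal: geometric means 1,286.8 and 1,728.5, a ratio of 1.34.
- Rank scale, if normal: P(X>Y) = Φ(420/(600√2)) = 0.69.

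One underlying effect can thus be reported as 420 kcal/day, 1.34 or 0.69, and the data choose which.

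**Energy requirement.** The target is 25 kcal/kg CBW without renal replacement or ECMO. With assumed heights of 1.55 m and 1.85 m at BMI 23, CBW is 23 × 1.55² = 55.3 kg and 23 × 1.85² = 78.7 kg. The targets are 1,381 and 1,968 kcal/day, a gap of about 590. This shows that the requirement can matter on the scale of the effect. It does not show how much variance it explains.

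**The case against.** The strongest reply is that little is at stake. A site-adjusted result is already promised for every outcome, so the dispute is largely over which analysis is called primary. On the trial's own figures power for 420 kcal/day is about 93% without adjustment. The error is conservative, and at an ICC near 0.02 the gain is negligible. All of that stands and limits the weight of the point. It does not remove it, because the headline interval would still come from an analysis that does not match the randomisation, on a scale fixed only after the data are seen.

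It can also be said that the outcome definition and sample size already imply kcal/day, and that a log or rank p-value does not prevent the mean difference from being reported. That is fair, but the normality rule covers all data with no exception for the primary outcome.

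A reader might infer more than the documents support:
- That covariates are chosen only from observed imbalance. The same sentence also names known covariates, and which ones they are may be left to a separate analysis plan.
- That body size is pure noise. Study PN is dosed per kg CBW, so the absolute effect may itself vary with body size. CBW is also set at BMI 23 for patients with a BMI of 25 or more, which narrows its spread.
- That enteral intake in the previous 24 hours is a strong predictor. It is capped near 80% by an exclusion criterion, and lower intake leads to a higher PN starting rate, which works against the association in the intervention arm.
- That days without feeding make the log analysis undefined. The primary outcome is a 7-day mean, which is zero only if nothing is delivered over the whole period.

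**Conclusion.** The point holds as a modest, cost-free improvement. The main comparison leaves out the stratification factor, and the effect scale of the primary result is left to a normality check. With an assumed ICC of 0.02, 0.10 or 0.20 the unadjusted standard error is too large by about 1%, 5% or 12%. At 0.10 or 0.20 the true level is about 3.6-3.9% or 2.8-2.9%. These sizes rest on the assumed ICC, on 600 being the total SD within an arm, and on equal allocation.

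A reader might conclude that the trial is underpowered or its test invalid. Neither follows: omitting site makes the test cautious rather than liberal, and power for 420 kcal/day is about 93% or more either way. No inflation of error from the normality check was calculated, and none is claimed. The objection to that check is that it leaves the estimated quantity open.

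**What to change.** For the primary outcome, replace the general rule with one named analysis: a linear model of 7-day mean energy in kcal/day with treatment, site and daily energy requirement at randomisation, all fixed in advance. Enteral intake in the previous 24 hours is an optional further covariate. If it is used, its slope may differ between arms. Report the adjusted mean difference with its 95% CI as the primary result.

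Drop the normality check as a gate for this outcome. With about 50 per arm, robust or bootstrap standard errors are enough if the data are skewed. Keep the unadjusted, log and rank analyses as named sensitivity analyses.

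The cost is a change of wording before the analysis. Site, energy requirement and prior intake are already needed for randomisation, the enteral target, eligibility and the PN starting rate, so no new data are collected. The site-adjusted model is already planned and only has to change places with the unadjusted test.
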